## Abstract

**Background:**

Radiotherapy of breast cancer can be associated with dermatitis. Grade ≥2 radiation dermatitis can be painful and impair the patients’ quality of life. To reduce the risk of this complication, patients have to perform skin care several times each day. This may require a considerable level of compliance. This randomized DAI-BREAC trial investigates whether a mobile application reminding the patients four times per day to perform skin care (reminder app) will contribute to reduction of grade ≥2 radiation dermatitis.

**Methods:**

This multinational, randomized, active-controlled, parallel-group, multicenter trial compares standard skin care supported by a reminder app (Arm A) versus standard skin care alone (Arm B) regarding grade ≥2 radiation dermatitis in patients receiving adjuvant radiotherapy for breast cancer. The effect of the app will be considered clinically relevant, if the rate of grade ≥2 radiation dermatitis is reduced from 25.4% (rate identified in a preceding study) to 15%. A total of 134 patients per arm including drop-outs are required. Secondary aims include pain (visual analogue scale), patient satisfaction with the app (questionnaire), impact of the app on the use of health technology (questionnaire), and benefit from support (coaching) by staff members regarding the use of the app (questionnaire).

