### Sample size {14}

The null hypothesis of equal rates of grade ≥2 skin toxicity is tested against the two-sided alternative hypothesis of different rates. Based on this hypothesis system, the sample size required for this trial is calculated considering the following assumptions:● A Chi-square Test will be applied● The two-sided significance level is set to 5%● In patients treated with hypo-fractionated radiotherapy for breast cancer, a retrospective pre-study suggested a rate of grade ≥2 dermatitis of 25.4% if standard skin care alone was administered [12].● Based on these retrospective data, a rate of grade ≥2 skin toxicity of approximately 30% was assumed in the reference group of a prospective trial, i.e. in patients receiving standard skin care alone for radiation dermatitis.● The impact of the Reminder App will be considered to be clinically relevant, if the rate of grade ≥2 dermatitis can be reduced to 15%.● The power to yield statistical significance if the difference in rates is in fact 15% is set to 80%.

Based on these assumptions, 131 patients are required per study arm within the Full Analysis Set. Considering that 2% of patients will not qualify for this set, a total of 268 patients should be randomized.

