In a previous retrospective study of our group that included 327 breast cancer patients irradiated in 2022 or 2023, 31.2% of the patients developed grade ≥2 radiation dermatitis [12]. Moreover, several factors showed highly or almost highly significant associations with the occurrence of grade ≥2 dermatitis on multivariate analysis, including history of chronic inflammatory disease (*p*=0.001), history of significant cardiovascular disease (*p*<0.001), smoking history of more than 10 pack years (*p*<0.001), normo-fractionated radiotherapy (*p*<0.001), and administration of a radiation boost (*p*<0.001). These risk factors were considered when designing the current DAI-BREAC trial. This randomized trial compares the rate of grade ≥2 radiation dermatitis with standard skin care plus a reminder app to the dermatitis rate with standard skin care alone in a cohort of 268 patients. If it is demonstrated that the reminder app contributes to a clinically relevant reduction of radiation dermatitis in breast cancer patients, such an app will likely become a useful tool for this group in the near future. When the final results of the DAI-BREAC trial will be available, a limitation of this trial should be considered, namely the fact that standard skin care practices may vary between the contributing centers. This article considered the items recommended to address in the SPIRIT 2013 checklist [16–18].

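### The abstract ties 134 patients per arm to a fall from 25.4% to 15%, but that number was derived for about 30% to 15%; for the abstract's effect, power is 50–56%

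*Protocol article*

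**What the plan says.** The Methods paragraph of the abstract sets clinical relevance at the point where the rate of grade ≥2 radiation dermatitis "is reduced from 25.4% (rate identified in a preceding study) to 15" per cent. Its next sentence gives 134 patients per arm, drop-outs included. It mentions neither a 30% control rate nor a power.

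The section Sample size {14} has both control rates, in separate bullets. It reports that "a retrospective pre-study suggested a rate of grade ≥2 dermatitis of 25.4% if standard skin care alone was administered". It then says that, on the basis of those data, "a rate of grade ≥2 skin toxicity of approximately 30% was assumed in the reference group of a prospective trial". The effect is clinically relevant "if the rate of grade ≥2 dermatitis can be reduced to 15" per cent. On power: "The power to yield statistical significance if the difference in rates is in fact 15% is set to 80" per cent. The result is 131 per arm in the Full Analysis Set and, after allowing 2% for patients outside that set, 268 randomized, which is 134 per arm.

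Eligibility criteria {10} admits only patients with an indication for hypo-fractionated radiotherapy, the group to which the 25.4% refers.

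**The concern.** One sample size is attached to two planned effects: 10.4 points in the abstract and 15 points in the sample size section. Both name 15% as the app-arm rate; they differ in the control rate from which the fall is measured. Since 131 per arm can give 80% power for only one of the two, one statement must be wrong.

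The abstract is the part most often read, and it sets the yardstick for the result. A reader who joins its 25.4% to 15% with the 80% in the sample size section will think the trial well powered for a 10.4-point fall. If controls behave like the protocol's own hypo-fractionated patients and the app arm reaches 15%, the trial would miss that fall in roughly 44–50% of repetitions. A non-significant result could then be given more weight against the app than it deserves.

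**Working it through.** **Inputs, all from Sample size {14} unless noted**
- Test: "A Chi-square Test will be applied".
- Level: "The two-sided significance level is set to 5" per cent, so z = 1.960.
- Power 80%, so z = 0.842.
- Allocation 1:1 (Sequence generation {16a}).
- Rates: 30% versus 15% (sample size section); 25.4% versus 15% (abstract).
- 131 per arm analysed; 2% loss.

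**Formula.** With control rate p₁, app rate p₂, their mean p̄ and d = p₁ − p₂:

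n per arm = [1.960·√(2p̄(1−p̄)) + 0.842·√(p₁(1−p₁) + p₂(1−p₂))]² / d²

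The continuity-corrected version is n' = (n/4)·[1 + √(1 + 4/(n·d))]².

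**Step 1: reproduce the plan's figure (30% versus 15%)**
- p̄ = 0.225 and d = 0.15. The two terms are 1.157 and 0.489, so n = (1.646/0.15)² ≈ 120.5, rounded up to 121.
- With the continuity correction, n' = 133.5, rounded up to 134.
- Exact power of Fisher's test, summing over both binomial distributions: 79.7% at 130 per arm and 80.1% at 131. So 131 is the number that Fisher's test gives for 80% power.
- Loss: 131/0.98 = 133.7, rounded up to 134 per arm; 2 × 134 = 268.

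The stated figures therefore reproduce for 30% versus 15%, on a Fisher basis.

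**Step 2: the same formulas for the abstract's effect (25.4% versus 15%)**
- p̄ = 0.202 and d = 0.104. The two terms are 1.113 and 0.474, so n = (1.587/0.104)² ≈ 233 per arm.
- With the continuity correction, 252 per arm.

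Neither is near 131.

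**Step 3: exact power at 131 per arm, two-sided 5%**

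| Control vs app | Uncorrected chi-square | Continuity-corrected | Fisher |
|---|---|---|---|
| 30% vs 15% | 83.7% | 79.6% | 80.1% |
| 25.4% vs 15% | 55.9% | 49.5% | 50.2% |
| 25.4% vs 12% | 80.4% | 75.8% | 76.1% |
| 25.4% vs 11.4% | 84.3% | 80.3% | 80.5% |

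The normal approximation for the uncorrected test agrees: 83.2% for the first row and 55.5% for the second.

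Read down one column at a time, power falls from 84% to 56% (uncorrected) or from 80% to about 50% (Fisher or corrected). With a 25.4% control rate, 80% power needs an app-arm rate of about 12% on the uncorrected basis, or about 11.4% on the other.

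**The case against.** The strongest reply is that the sizing itself contains no error. The sample size section discloses both 25.4% and 30%, attaches its 80% only to a true 15-point difference, and reproduces from its own inputs. The abstract states no power, so it promises none for 25.4% versus 15%. On this view the defect is one sentence of summary. That stands as to where the error lies. It does not remove the error, because the abstract still presents 134 per arm as the number required for a 10.4-point fall.

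A second reply is that planning at 30%, above a retrospective 25.4%, is a disclosed judgement. That also stands. Which rate the controls will show cannot be settled from the protocol.

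Two stronger readings are tempting. A reader might infer that power is 56% where the plan claims 80%. That mixes methods: 56% belongs to the uncorrected test, under which design power is 84%, while 131 gives 80% only under Fisher's test or, nearly, a continuity correction, under which the matching figure is about 50%. A reader might also infer that 30% was borrowed from the whole retrospective cohort, of which the Discussion says that "31.2% of the patients developed grade ≥2 radiation dermatitis", with normo-fractionated radiotherapy among its risk factors. The sample size section does not cite that rate; it bases the 30% on the data that gave 25.4%. The link is conjecture.

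**Conclusion.** The point holds as a contradiction between the abstract and the sample size section, with the error in the abstract. The sample size of 131 per arm (134 with losses) supports about 30% to 15% and does not support 25.4% to 15%, for which 80% power would need 233 to 252 per arm before losses.

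If the control rate is 25.4% and the app-arm rate 15%, power is about 50–56%, depending on the test. This assumes 131 analysed patients per arm, a two-sided 5% level and an unadjusted comparison of two independent proportions. The scenario deserves stating because 25.4% is the protocol's own figure for the eligible population; nothing in the document shows that it will be the control rate in the trial. The documents do not support calling the sample size calculation wrong or the trial mis-sized for its stated 30% assumption.

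**What to change.** 1. In the abstract, give the planned effect as a reduction from about 30% to 15%, matching Sample size {14}. The 25.4% may stay if it is labelled as the retrospective rate and not as the planning baseline.
2. In Sample size {14}, add that with 131 per arm power is about 50–56%, depending on the test, if the control rate is 25.4% and the app-arm rate 15%, and that 80% power would then need an app-arm rate of about 11.4–12%. Name the test behind each figure, so that an uncorrected figure is not set beside an 80% obtained with Fisher's test.

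The cost is a few sentences and a less favourable stated power. Neither the sample size nor the conduct of the trial needs to change.

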**Discussion:**

If the reminder app contributes to a decrease of grade ≥2 radiation dermatitis in patients irradiated for breast cancer, it will likely become a useful instrument for these patients.

**Trial registration:**

Clinicaltrials.gov (NCT06483477; URL: https://clinicaltrials.gov/show/NCT06483477). Registered on 1st of July, 2024. First patient was included in December 2024.

## Administrative information

Note: the numbers in curly brackets in this protocol refer to SPIRIT checklist item numbers. The order of the items has been modified to group similar items (see http://www.equator-network.org/reporting-guidelines/spirit-2013-statement-defining-standard-protocol-items-for-clinical-trials/).

## Introduction

### Background and rationale {6a}

Many breast cancer patients receive adjuvant radiotherapy following breast conserving surgery or mastectomy [1, 2]. Radiotherapy of breast cancer can be associated with acute toxicities including radiation dermatitis. Grade ≥2 dermatitis can be painful and impair the patients’ quality of life [3, 4]. To reduce the risk of radiation dermatitis, the patients are asked to perform skin care several times per day during their radiotherapy course and afterwards, which may require a high level of discipline. In a randomized trial of patients irradiated for head-and-neck cancer, daily reminders by medical staff members to perform skin care appeared to increase the patients’ compliance resulting in less acute dermatitis [5]. Subsequently, the question has been raised whether the daily reminders by medical staff members could be replaced by a mobile application (reminder app) reminding the patients several times daily to perform skin care. This hypothesis was investigated in another prospective trial that compared standard skin care supported by a reminder app and standard skin care alone in patients with head-and-neck cancer [6]. That trial was prematurely terminated because only 56 of 168 patients were recruited due to slow accrual. At this stage, the reminder app has led to a non-significant reduction of grade ≥2 dermatitis. Reasons for slow accrual included the facts that many patients screened for eligibility had no smartphone or refused to participate in the trial.

These reasons were considered to be more pronounced in patients with head-and-neck cancer than in patients with breast cancer. In a previous prospective study, sleep disorders during a radiotherapy course and the role of smartphones or tablets in breast cancer patients were investigated [7]. The proportion of screened patients participating in this trial was significantly greater than 90%. Therefore, it was decided to additionally investigate a reminder app in a cohort of breast cancer patients. In the present DAI-BREAC trial, a reminder app will be prospectively tested that reminds breast cancer patients four times each day to perform the required skin care. This will likely contribute to the reduction of grade ≥2 radiation dermatitis in these patients.

### Objectives {7}

The main goal of this randomized trial is to evaluate whether standard skin care supported by a reminder app is superior to standard skin care alone with respect to prevention of grade ≥2 radiation dermatitis in patients receiving adjuvant radiotherapy for breast cancer. Secondary aims include pain (radiation fields), patient satisfaction with the reminder app, impact of the reminder app on the use of health technology, and benefit from support (coaching) by staff members regarding the use of the reminder app.

### Trial design {8}

This is a multinational, randomized, active-controlled, open-label, multicenter, parallel-group trial, which compares the following treatments of radiation related skin toxicity in patients with breast cancer:

Standard skin care supported by a reminder app (Arm A) vs. standard skin care alone (Arm B).

## Methods: Participants, interventions and outcomes

### Study setting {9}

The study will be performed in Germany (one university hospital, two academic teaching hospitals, one private practice) and Denmark (one university hospital). Participating sites can be seen at clinicaltrials.gov.

### Eligibility criteria {10}

Inclusion criteria1.Histologically proven invasive breast cancer2.Indication for adjuvant hypo-fractionated radiotherapy [8, 9]3.Possession of and ability to use a smartphone4.Female gender5. Age ≥18 years6.Written informed consent7.Capacity of the patient to consent

Exclusion criteria1.Pregnancy, Lactation2.Expected non-compliance

Male patients were not included, since male breast cancer is increasingly considered a separate tumor entity with a biological behavior different from female breast cancer [10]. Radiation dermatitis will be assessed by an experienced observer (specially trained nurse, technician, or physician) different from the person who performs the routine visit of the patient (“blinded observer concept”), at the start of radiotherapy, weekly during the course of radiotherapy, and at the end of radiotherapy.

### Who will take informed consent? {26a}

Informed consent will be taken by specially trained physicians registered as investigators for this trial.

### Additional consent provisions for collection and use of participant data and biological specimens {26b}

Additional collection and use of participant data or biological specimens are not planned.

### Interventions

#### Explanation for the choice of comparators {6b}

In a previous randomized trial of patients irradiated for head-and-neck cancer, daily reminders by staff members regarding skin care likely improved the patients’ compliance, which resulted in less radiation dermatitis [5]. A subsequent randomized trial investigating whether the daily reminders could be replaced by a mobile application (reminder app) failed to showed a significant impact, possibly because the trial was prematurely terminated due to slow accrual [6]. Since breast cancer patients often show a great interest to participate in a clinical trial, it was felt that the recruitment for a randomized trial investigating the impact of a reminder app on grade ≥2 radiation dermatitis would be more successful in this patient group [7].

### Intervention description {11a}

#### Standard skin care

In both the experimental arm (A) and the control arm (B) standard skin care has to be performed by the patient from the start of radiotherapy. The patients are supposed to perform the skin care four times a day. Standard skin care may vary at the participating centers. At the University of Lübeck, it includes fatty cream with 2-10% urea (fatty cream alone, if patients do not tolerate urea) and, in case of pruritus, addition of mometasone furoate cream.

#### Reminder App

In addition, patients of Arm A are supported by a Reminder App, which is developed by the professional company Nextlabel OHG from Lübeck. The purpose of the app is to remind the patients in an intuitive, unobtrusive and supportive way to perform skin care. By default, patients are reminded four times a day, but they will also be able to define a notification schedule that best suits their personal needs. The patients may postpone each required care procedure for up to 2 hours. With each procedure, the patients are guided through the skin care with simple and self-explanatory illustrations. To increase the patients’ motivation, they will additionally earn points for regular and punctual performed care procedures. The patients receive a hand-out including instructions how to properly perform skin care, but they can also find an information page within the application that includes similar instructions.

### Criteria for discontinuing or modifying allocated interventions {11b}

In case of grade ≥2 moist desquamation or grade ≥3 radiation dermatitis, each day antiseptic agents will be administered for wound cleansing followed by administration of silicon or calcium alginate bandage in patients of both arms. This treatment will be continued until moist desquamation radiation disappears and radiation dermatitis improves to grade 2.

### Strategies to improve adherence to interventions {11c}

Patients will be seen by staff members (radiotherapy technologists) of the treating Department of Radiation Oncology during each treatment session and additionally by investigators of the trial once a week.

### Relevant concomitant care permitted or prohibited during the trial {11d}

Please, refer to 11 b. If required, any type of concomitant care and interventions are permitted during the trial for treatment of other radiotherapy- or radio-chemotherapy-related toxicities and co-morbidities not related to radiotherapy or radio-chemotherapy.

### Provisions for post-trial care {30}

Following the end of radiotherapy (end of study), the study participants receive the standard follow-up program for breast cancer patients. Harm from trial participation is not expected, since all participating patients receive the same anticancer treatment as they would have received if not participating.

### Outcomes {12}

Primary endpoint is the rate of grade ≥2 radiation dermatitis (CTCAE v5.0) at the end of radiotherapy [11].

In addition, the following endpoints will be evaluated:1.Pain (radiation fields): Evaluation prior to, weekly during, and at the end of radiotherapy2.Patient satisfaction with the reminder app (Arm A): Evaluation at the end of radiotherapy3.Impact of the reminder app on the use of health technology (Arm A): Evaluation at the end of radiotherapy4.Benefit from support (coaching) by staff members (Arm A): Evaluation at the end of radiotherapy

### Participant timeline {13}

The five centers that are planned to participate aim to include an average of 27 patients per year. Thus, the recruitment of all 268 patients should be completed within 24 months. Since the treatment period will be 3 to 4 weeks, the total running time for the trial is expected to be 25 months. Regarding the timeline of trial procedures and assessments, please see Figure 1.

**Fig 1 Fig1:**
[figure not shown]
Schedule of enrolment, interventions and assessments

### Sample size {14}

The null hypothesis of equal rates of grade ≥2 skin toxicity is tested against the two-sided alternative hypothesis of different rates. Based on this hypothesis system, the sample size required for this trial is calculated considering the following assumptions:● A Chi-square Test will be applied● The two-sided significance level is set to 5%● In patients treated with hypo-fractionated radiotherapy for breast cancer, a retrospective pre-study suggested a rate of grade ≥2 dermatitis of 25.4% if standard skin care alone was administered [12].● Based on these retrospective data, a rate of grade ≥2 skin toxicity of approximately 30% was assumed in the reference group of a prospective trial, i.e. in patients receiving standard skin care alone for radiation dermatitis.● The impact of the Reminder App will be considered to be clinically relevant, if the rate of grade ≥2 dermatitis can be reduced to 15%.● The power to yield statistical significance if the difference in rates is in fact 15% is set to 80%.

Based on these assumptions, 131 patients are required per study arm within the Full Analysis Set. Considering that 2% of patients will not qualify for this set, a total of 268 patients should be randomized.

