### Assignment of interventions: allocation

#### Sequence generation {16a}

The patient identification number will consist of four digits (one digit for the contributing center and three digits for the consecutive patient number). After registration, patients will be randomized in a 1:1 ratio to receive either standard skin care supported by a reminder app (Arm A) or standard skin care (Arm B) for treatment of radiation related skin toxicity. Allocation of a patient to a treatment arm will be performed in the form of a stratified block-randomization with random block size using an electronic case report form (eCRF).

Stratification will be done using the following prognostic factors:1.Treatment volume: Breast or chest wall alone vs. breast or chest wall plus lymph nodes2.Radiation boost: Yes vs. no3.At least one risk factor of dermatitis: Yes vs. no (Risk factors include chronic inflammatory disease, significant cardiovascular disease, and smoking history of >10 pack years.)

The corresponding document will be kept at the institution which performs the randomization until the end of the study. Afterwards, the original randomization list will be kept in the trial master file at the trial center of the coordinating investigator for a minimum of 10 years after the final report. The randomization will be performed via eCRF centrally by an external company using its standard software. The randomization process is based on this company’s standard operating procedures (SOPs). Once the randomization is allocated to the patient it cannot be changed.

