### Statistical methods

#### Statistical methods for primary and secondary outcomes {20a}

All data recorded in the eCRFs describing the study population and toxicity will be analyzed descriptively. Categorical data will be presented in contingency tables with frequencies, percentages and their 95% confidence intervals. Continuous data will be summarized with at least the following: frequency (n), median, quartiles, mean, standard deviation (standard error), minimum and maximum. Number of patients with protocol deviations and listings describing the deviations will be provided. In general, chi-square tests will be used to compare percentages in a two-by-two contingency table, replaced by Fisher´s exact test if the expected frequency in at least one cell of the associated table is less than 5. Stratified two-by-two contingency tables will be analyzed using Cochran-Mantel-Haenszel tests. Logistic regression models serve as multivariable methods for binary endpoint data. Comparison of ordinal variables between treatment arms will be performed using the asymptotic Wilcoxon-Mann-Whitney test, replaced by its exact version in case of ordinal categories with small number of categories and/or sparse data within categories. Any shift in location of quantitative variables between study groups will be performed with Wilcoxon-Mann-Whitney tests. Time-to-event data will be analyzed by Kaplan-Meier methods, when merely non-informative censoring occurs. For statistical comparison, the log rank-test will be provided supplemented by multivariate Cox proportional hazards models. The data analysis will be performed according to the SAP finalized prior to database lock and prior to any statistical analysis.

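### The only test tied to the primary hypothesis is an unadjusted chi-square although randomisation is stratified on prognostic factors: valid, but mildly conservative, and free to improve

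*Protocol article*

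**What the plan says.** Protocol article, Sample size {14}: the null hypothesis of equal grade ≥2 rates is set against a two-sided alternative, followed by a list of assumptions. The first is "A Chi-square Test will be applied". The others that matter here are "The two-sided significance level is set to 5" percent; "a rate of grade ≥2 skin toxicity of approximately 30% was assumed in the reference group of a prospective trial"; clinical relevance "if the rate of grade ≥2 dermatitis can be reduced to 15" percent; and "The power to yield statistical significance if the difference in rates is in fact 15% is set to 80" percent. The result is 131 patients per arm in the Full Analysis Set and 268 randomised.

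Protocol article, Sequence generation {16a}: block randomisation is stratified. "Stratification will be done using the following prognostic factors" introduces treatment volume, boost, and at least one dermatitis risk factor. Three binary factors make eight strata.

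Protocol article, Statistical methods {20a}: "In general, chi-square tests will be used to compare percentages in a two-by-two contingency table", with Fisher's exact test for small expected counts. The section then lists CMH for stratified two-by-two tables and logistic regression for binary endpoints. It links none of these to the primary endpoint, does not say that the stratification factors enter the primary comparison, and refers the analysis to an SAP finalised before database lock.

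Protocol article, Discussion: in a retrospective cohort of 327 patients with 31.2% grade ≥2 dermatitis, boost, cardiovascular disease and smoking history have p<0.001 and chronic inflammatory disease p=0.001. No odds ratios or prevalences are given, and treatment volume is not among the factors listed.

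**The concern.** Stratifying on prognostic factors makes the arms alike on those factors, so the true variance of the difference in rates is smaller than under simple randomisation. The unadjusted chi-square does not use this. Its variance still includes the spread of risk between strata, which the design has largely removed from the comparison. The test then rejects less than 5% of the time under the null and has less power than a test that works within strata. The Discussion says the risk factors were considered in the design, but the one test named for the primary hypothesis does not use them.

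Two things are at stake: a small amount of power that could be had without extra patients, and clarity. Chi-square, CMH and logistic regression are all listed, and the trial is open-label, so it should be plain which one decides the primary result.

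**Working it through.** **1. The plan's own figure.** With p1 = 0.30, p2 = 0.15, mean 0.225, two-sided 5% and 80% power:

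n = [1.960·√(2·0.225·0.775) + 0.842·√(0.30·0.70 + 0.15·0.85)]² / 0.15² = (1.157 + 0.489)² / 0.0225 ≈ 120.5, so 121 per arm.

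The continuity-corrected version gives 134. Exact enumeration for Fisher's test gives 79.7% power at 130 and 80.1% at 131, which matches the stated 131. Then 131/0.98 = 133.7, so 134 per arm and 268 in total. The sizing is therefore slightly generous for a plain chi-square. At 131 per arm the uncorrected chi-square has 83.2% power by formula and 83.7% by enumeration.

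**2. Why stratification makes the chi-square conservative.** The chi-square uses variance p(1−p) per patient. With arms balanced within strata, the true variance is the weighted within-stratum part, Σ w_s p_s(1−p_s).

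Worked example under the null at 30%, with assumed inputs: treatment volume not prognostic, boost prevalence 50%, risk-factor prevalence 40%, odds ratio 3 for each.

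- Neither factor: weight 0.3, odds 1/7, risk 0.125.
- One factor: weight 0.5, odds 3/7, risk 0.300.
- Both factors: weight 0.2, odds 9/7, risk 0.5625.
- Mean risk: 0.0375 + 0.150 + 0.1125 = 0.300.
- Within-stratum variance: 0.3·0.125·0.875 + 0.5·0.3·0.7 + 0.2·0.5625·0.4375 = 0.187. Chi-square variance: 0.3·0.7 = 0.210. Ratio 0.891.
- True size: 2·[1 − Φ(1.960/√0.891)] = 2·[1 − Φ(2.077)] ≈ 3.8%.

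**3. Simulation with near-perfect balance.** 262 patients, eight strata balanced to within one patient, 100,000 trials per row, assumed prevalences 30% (volume), 50% (boost), 40% (risk factor). Entries are chi-square / CMH.

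| Odds ratios (volume, boost, risk) | Size at null rate 30% | Power at 30% vs 15% |
|---|---|---|
| 1, 1, 1 | 5.1% / 5.1% | 83.8% / 83.7% |
| 1, 2, 2 | 4.5% / 5.0% | 84.1% / 85.0% |
| 1, 3, 3 | 3.8% / 5.0% | 85.0% / 87.1% |
| 1, 4, 4 | 3.3% / 5.0% | 85.6% / 88.7% |
| 2, 2, 2 | 4.5% / 5.1% | 84.4% / 85.7% |
| 3, 3, 3 | 3.3% / 4.9% | 85.4% / 88.2% |
| 4, 4, 4 | 2.8% / 4.9% | 86.1% / 90.3% |

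The row 1, 3, 3 agrees with the hand calculation. With lower prevalences (20%, 30%, 25%) the pattern is the same. The last row, with all three factors at 4, is an extreme. Near-perfect balance makes the conservatism shown here an upper bound for block randomisation.

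**4. Simulation with permuted blocks of 2, 4 and 6.** Incomplete blocks are allowed; assumed prevalences 30%, 50%, 35%. Chi-square / CMH:

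| Odds ratios (volume, boost, risk) | Power at 30% vs 15% | Power at 25.4% vs 15% |
|---|---|---|
| 1, 2.2, 2.2 | 84.5% / 85.5% | 56.7% / 58.3% |
| 1, 3, 3 | 85.0% / 87.0% | 56.0% / 59.3% |
| 2, 3, 4 | 85.2% / 88.3% | 56.7% / 61.8% |

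Chi-square size in the first two rows is 4.3% and 3.9%, against 5.0% for CMH. The gains from CMH are 1.0 to 3.1 points at 30% vs 15% and 1.6 to 5.1 points at 25.4% vs 15%.

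**5. Are such odds ratios plausible?** In 327 patients with 31.2% events, the smallest unadjusted odds ratio giving a Wald p of 0.001 is about 2.2 at 40–50% prevalence, 2.3 at 30% and 3.5 at 10%. The reported p-values therefore point to estimates of about 2 or more. This is a rough guide: the reported p-values are multivariable, significant estimates tend to be inflated, the cohort included normo-fractionated patients, and the trial stratifies on a composite of the risk factors.

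**The case against.** The strongest reply is that the protocol has not committed itself to the unadjusted test. The chi-square sentence is one of a list of sample-size assumptions, and sizing on a simple test while analysing with a stratified one is common. Statistical methods {20a} makes CMH available, and the SAP, which is not shown, may name it. This stands: a reader might infer that the wrong test is locked in, and the documents do not support that. What remains is that the protocol connects one test, and only one, to the primary hypothesis, and that this test does not use the stratification.

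The chi-square is also valid: its type I error is at or below 5%. It is simple and addresses the marginal difference used for sizing. A reader might conclude that it has no merit or that its result would be unsound; neither follows.

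Nor does it put the planned power at risk. At 30% vs 15% it stays at 84% to 86% in the simulations. The roughly 56% power at 25.4% vs 15% (the contrast given in the Abstract) comes from the lower control rate, and CMH does not repair it.

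The magnitudes depend on assumed odds ratios and prevalences. If the factors were not prognostic, CMH would gain nothing.

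Finally, a reader might extend the point to centre, because "Standard skin care may vary at the participating centers". That is not pressed. Eight strata in five centres would make 40 cells for 268 patients, so leaving centre out of the stratification is defensible, and the Discussion already names varying skin care as a limitation.

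**Conclusion.** The point holds as a modest inefficiency and a lack of clarity, not as a threat to validity. The direction is certain if the stratification factors are prognostic, which the protocol itself asserts and its Discussion supports for boost and the individual risk factors, though not for treatment volume. For assumed odds ratios of about 2 to 4, the chi-square's true size is roughly 3% to 4.5%. Its power is about 1 to 3 points below CMH at 30% vs 15% and about 2 to 5 points below at 25.4% vs 15%. The planned 80% at 30% vs 15% is met with either test. The exact loss cannot be derived from the documents.

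**What to change.** State in the protocol and SAP, before database lock, that the primary analysis is the CMH test over the eight randomisation strata, reported with the Mantel-Haenszel risk difference and its 95% CI. Keep the unadjusted chi-square as a sensitivity analysis. If the SAP already names CMH, amend Sample size {14} to say that the chi-square was used for sizing only and refer to the SAP for the primary test.

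The cost is about one sentence in each document. The stratification data are already collected at baseline, CMH is already among the listed methods, and the sample size does not change.
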